#### Objective 2: Conduct a preliminary test of the nursing discharge teaching intervention

Descriptive statistical analyses of all variables will be conducted to obtain means and standard deviations for continuous variables and proportions for categorical variables. Assessment of differences in patient activation, health confidence, readiness for hospital discharge, experience with discharge care and readmission rates between pre and post-test participants will be undertaken through comparison tests (Student’s *t* test and chi-square test). Effect size and confidence interval of the intervention will be estimated to be able to calculate the sample size for future efficacy studies [67]. Effect size of the intervention will be estimated with a linear regression model of level of patient activation and health confidence at discharge on levels measured at admission. The adjusted model will include following variables: age, sex, level of education and number of chronic diseases. In light of our sample size, effect size will be interpreted with consideration of both the magnitude and *p* value [68]. All analyses will be carried out using Stata 16 computing software [69].

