## Method

### Study design

This study is a pragmatic feasibility study using a two group pre/post-intervention comparative design. This protocol is presented as per the SPIRIT (Standard Protocol Items: Recommendations for Interventional Trials) guideline and Thabane and Lancaster’s guidance on how to report protocols of pilot and feasibility trials [32, 33]. All elements of the SPIRIT checklist adapted with the CONSORT extension are reported in Additional file 1. This study has been approved by the Cantonal Ethics Committee Vaud (2020-00141). Written informed consent will be obtained from eligible patients by the researcher. Nurses participating in the study will receive an information sheet and be asked for written consent.

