### Participants and recruitment

A sample of 12–15 nurses (4–5 per unit) will be recruited on a voluntary basis to take part in the study. Their participation will involve being trained in the intervention, delivering it during the implementation phase, participating in qualitative and quantitative evaluations in the pre- and post-implementation phase of their teaching behaviours and feasibility of the intervention. Inclusion criteria for nurse participants will be registered nurses, employed full time (80–100% work rate).

Inclusion criteria for participants will be 50 years old or more, having two or more chronic conditions, being hospitalized for more than 48 h, an expected discharge home defined at the beginning of the hospitalization and fluent speaking, reading and writing in French [34]. The inclusion criterion of 50 and over was chosen because from this age onwards the prevalence of multimorbidity is constantly increasing [35]. These criteria are deliberately broad in order to obtain a sufficient diversity of patients to reflect the variations encountered in patients in real-world practice. Patients will be excluded if they are cognitively unable to give their informed consent.

As this is a feasibility study, there is no sample size calculation [36]. A convenience sample of 180 hospitalized patients (90 pretest/90 posttest) was determined based on an estimate of the number of patients meeting the criteria for inclusion in the medical units of 30 patients per unit month. With an estimated recruitment rate of 50%, 30 pretest and 30 posttest patients per unit could be recruited over a 2-month period to achieve the 180-patient sample. Pretest participants will be recruited before nurses’ training about discharge teaching to prevent contamination. All eligible patients will be informed about the study and recruited four preselected days per week in two sites and 2 days per week in the third site due to resources’ constraints. Patients in the control and intervention groups will be recruited within 2 days after admission. Patients eligible to participate will be identified by the units’ nurses trained on participants’ inclusion and exclusion criteria. They will routinely screen newly admitted inpatients and inform the researcher of eligible patients. During recruitment days, all eligible patients will be informed about the study and asked for participation.

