### Study procedure

Patients’ outcomes will be measured during a control period with patients receiving usual care, followed by outcomes measurements during the implementation period with patients receiving the discharge teaching intervention. The discharge teaching intervention will be implemented as an enhancement to usual care provided to patients hospitalized on the study units and therefore requires change/improvement in nurses’ teaching behaviours to achieve successful outcomes of the teaching intervention. The plan for implementation by clinical nurses of the discharge teaching intervention is based on the Theoretical Domains Framework (TDF) and the Behavior Change Wheel (BCW) of the COM-B model [31, 37].

The TDF consists in 14 domains identifying influences on health professional behaviour [37]. This framework will be used to identify which domains should be prioritized in implementation approaches to change nurses’ behaviours. These interventions will be informed by the BCW, which is a synthesis of 19 frameworks of behaviour change comprising nine intervention functions [31]. Intervention functions are broad categories of interventions that can change nurses’ behaviours [31]. To develop the implementation plan, we will rely on the four-step method proposed by French et al. [30, 38]. These are identifying the problem, assessing the problem, forming possible solutions and evaluating the selected intervention. Details of steps 1–4 are presented in Fig. 1 and Additional files 2 and 3.

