##### Sociodemographic and medical characteristics

The following baseline participants sociodemographic and health data will be collected from health electronic records and reported in a REDCap™ electronic case report form (eCRF): age, sex, number of chronic conditions, years living with a chronic disease, length of stay and use of home health care services before and after index hospitalization. To determine the number of chronic conditions, a list of 75 chronic conditions most relevant in multimorbidity and developed by experts in Switzerland will be used to retrieve data on chronic conditions from discharge data from electronic records and coded as 1=the condition is present and 0= the condition is absent [64]. Total number of chronic conditions will be calculated for each patient. Number of previous hospitalizations in the same hospital within the last year will be retrieved from administrative hospitalization data and patients will be asked for information about prior hospitalization in a different hospital. As cohabitation and education are usually not specified in health electronic records, these questions will be asked directly to the participants.

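### Readiness for discharge and discharge experience get only unadjusted t tests between sequential, non-randomised cohorts, while activation and health confidence are covariate-adjusted

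*Protocol article*

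**What the plan says.** **Design.** The Study design section states: "This study is a pragmatic feasibility study using a two group pre/post-intervention comparative design". The groups follow one another in time (Study procedure): "Patients’ outcomes will be measured during a control period with patients receiving usual care, followed by outcomes measurements during the implementation period".

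**Sample.** Participants and recruitment states "As this is a feasibility study, there is no sample size calculation [36]" and fixes the number from recruitment capacity: "A convenience sample of 180 hospitalized patients (90 pretest/90 posttest)".

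**Tests.** Data analysis, Objective 2, covers five patient outcomes in one sentence. It begins with activation and health confidence and continues: "readiness for hospital discharge, experience with discharge care and readmission rates between pre and post-test participants will be undertaken through comparison tests". The methods named are Student's t test and the chi-square test. For scale scores such as RHDS-SF and DICARES this means the t test.

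**Adjusted model.** The same paragraph specifies one regression. It models activation and health confidence at discharge on their admission levels, with age, sex, education and number of chronic diseases in the adjusted version. No adjusted analysis is given for RHDS-SF or DICARES.

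**Covariates at hand.** The section on sociodemographic and medical characteristics collects all four of those variables, and also years with chronic disease, earlier home care and cohabitation. It adds: "Number of previous hospitalizations in the same hospital within the last year will be retrieved from administrative hospitalization data".

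**The concern.** In a before-after comparison of different patients, the crude difference is the intervention effect plus whatever the change in patient mix contributes. The protocol acts on this for activation and health confidence, which have an admission measurement to condition on as well as four covariates. RHDS-SF and DICARES have less protection to begin with. DICARES is taken by telephone 7 to 10 days after discharge and RHDS-SF concerns readiness to leave, so neither has an admission value. Yet these are the outcomes left unadjusted.

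The documents allow several routes to a systematic shift, though they do not show that one will occur:
- Unit nurses identify eligible patients in both periods, and the nurse training falls between the periods.
- Eligibility includes a judgement that the patient is expected to go home.
- The three units differ in size and type, and recruit on different numbers of days per week.

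At stake is whether a difference in readiness or discharge experience can be read as a signal of the intervention. The article plans tests on both outcomes as part of its preliminary test.

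**Working it through.** **1. The plan's own figure.** The inputs are "inclusion in the medical units of 30 patients per unit month", 50% recruitment, two months per period, three units and two periods.
30 × 0.5 × 2 × 3 = 90 per period, and 90 × 2 = 180. The stated sample is reproduced. It rests on capacity, so there is no planned power or effect size to check against.

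**2. Precision of the crude comparison.** In SD units, SE = sqrt(2/n).
- n = 90: SE = sqrt(2/90) = 0.149; 95% CI half-width = 1.96 × 0.149 = 0.29 SD.
- n = 72 (20% loss, the article's feasibility limit): SE = sqrt(2/72) = 0.167; half-width 0.33 SD.

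**3. Bias from a case-mix shift.** Take one covariate whose mean differs systematically between periods by d SD and whose within-group correlation with the outcome is r. With no true effect, the crude difference is centred on r × d. Both inputs are assumptions; neither is in the documents. With r = 0.3:
- d = 0.2: bias 0.3 × 0.2 = 0.06 SD
- d = 0.3: bias 0.09 SD
- d = 0.4: bias 0.12 SD

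**4. Effect on the nominal 5% test.** Rejection rate = Φ(b/SE − 1.96) + Φ(−b/SE − 1.96), with b the bias.

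| Bias (SD) | b/SE, n = 90 | Rejection rate, n = 90 |
|---|---|---|
| 0.06 | 0.40 | 6.9% |
| 0.09 | 0.60 | 9.3% |
| 0.12 | 0.80 | 12.7% |

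At n = 72, a bias of 0.06 SD gives 6.5%. A bias of 0.12 SD gives b/SE = 0.72 and Φ(−1.24) + Φ(−2.68) = 11.1%.

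**5. Cost of adjusting.** Ratio of adjusted to crude SE ≈ sqrt((1 − r²)(1 + d²/4)). For r = 0.3 and d = 0.2 this is sqrt(0.91 × 1.01) = 0.96; for d = 0.4 it is sqrt(0.91 × 1.04) = 0.97. Adjusting for that covariate removes its bias and loses no precision.

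**6. Why readmission is set apart.** The window is 7 days. At assumed rates of 2% to 10%, 180 patients yield 180 × 0.02 = 3.6 to 180 × 0.10 = 18 events. With group plus four covariates that is 3.6/5 = 0.7 to 18/5 = 3.6 events per parameter, too few for an ordinary adjusted model.

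**The case against.** The strongest reply is that this is a feasibility study. It has no sample size calculation and calls its test preliminary. The feasibility thresholds in its text concern recruitment, loss to follow-up and completion of measures, not p-values. Both periods also use the same units and criteria, with equal targets per unit, and all eligible patients on recruitment days are approached. If the targets are met, unit is balanced by design. The larger threat, calendar time, cannot be adjusted away.

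Most of this stands, and it limits how much the point matters. It does not remove it. The tests are planned, the article itself thought adjustment worthwhile for two outcomes in the same comparison, and it names a weaker method for the other two rather than leaving the method open.

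Four stronger readings are tempting, and the documents do not support them.
- **Unadjusted estimates will size the next trial.** A reader might infer this because the sentence on effect size and future sample size names no outcome. The model that follows covers only activation and health confidence, so the link is firm for those two alone.
- **Readmission should be adjusted too.** The likely event count does not allow it (step 6).
- **The error rate could be far higher.** A bias of 0.15 SD would give 17.2%, but it lies outside the 0.06 to 0.12 SD range assumed here, and nothing in the documents points to it.
- **Chance imbalance alone creates the problem.** The t test's standard error already allows for chance imbalance. Only a systematic shift biases the comparison.

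**Conclusion.** The point holds for RHDS-SF and DICARES, as a correctable inconsistency of moderate weight. Within one non-randomised comparison, two outcomes are adjusted for measured case mix, while two with no admission value are not, although the covariates are collected.

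Under the assumed inputs the bias is 0.06 to 0.12 SD and the false-positive rate about 7 to 13% at 90 per group. The bias is smaller than the 0.29 SD half-width of the confidence interval, so it would distort a preliminary signal rather than dominate it. The size depends wholly on the assumed shift and correlation. If the case mix does not move between periods, the crude test is not biased by it.

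**What to change.** Make a linear model the main estimate for RHDS-SF and DICARES, and report the crude difference beside it.
- **Core terms:** group, plus the article's own covariates (age, sex, education, number of chronic diseases).
- **Preferably also:** unit, admission health confidence and previous hospitalisations.
- **Leave out:** length of stay and home care after the index stay, which arise after enrolment. Chronic conditions are coded from discharge data, so state that they are used as a marker of pre-existing disease.
- **Readmission:** report counts and a risk difference with confidence interval, without a multivariable model.
- **Limitation to state:** adjustment handles measured case mix only, and does not remove calendar-time or unmeasured differences between the periods.

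The cost is a change of wording in the analysis section. No new data, patients or visits are needed.

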## Discussion

This paper presents a study protocol for judging the feasibility of a nursing discharge teaching intervention for inpatients with chronic conditions in French-speaking Swiss hospitals. Adopting a pragmatic approach, the planned feasibility study has the potential to generate a better understanding of how an intervention can be implemented and tested in “real-world” clinical practice [70]. Most of nursing activities are guided by descriptive frameworks of interventions, prescribing what nurses should do. The discharge teaching intervention proposed in this study differs precisely because it has been developed on the basis of an explanatory model of how discharge teaching works and under what circumstances [39].

The proposed innovative discharge teaching intervention uses the patient activation concept and patients’ life situation to individualize and better tailor the teaching. Taking these factors into account is expected to contribute to changes in how nurses prepare patients for discharge. In addition, this study will also generate new knowledge in the patient teaching field because the activation concept has not yet been applied in the context of preparation for discharge from an acute hospitalization. Results will therefore contribute to determining whether older and multimorbid inpatients could benefit from applying the concept of patient activation to discharge teaching.

As implementation of discharge teaching remains unsatisfactory in French-speaking Switzerland, a preliminary step appears necessary to enhance nurses’ awareness about the importance of discharge teaching [27]. Any intervention to improve discharge process would certainly fail without targeting a practice change in discharge teaching. The use of an implementation framework will help us to generate an understanding of factors at nurses’ individual level that contribute to the success or failure of the intervention implementation. Thus, understanding how to successfully implement discharge teaching in the real-world practice will help to remove obstacles often encountered when implementing interventions initially tested in highly controlled conditions, in the real-world practice. Results will inform future design of a hybrid type II trial to determine effectiveness of the discharge teaching intervention and implementation approaches [29].

## Data Availability

Not applicable

## Abbreviations

AIM: Acceptability of Intervention Measure
BCW: Behavior Change Wheel
CMO: Context-Mechanism-Outcomes
CS-PAM: Clinician Support for Patient Activation Measure
DIBQ: The Determinants of Implementation Behavior Questionnaire
DICARES: Discharge Care Experiences Survey
eCRF: Electronic case report form
FIM: Feasibility of Intervention Measure
HCS: Health Confidence Score
IAM: Intervention Appropriateness Measure
ICAN: Instrument for Patient Capacity Assessment
MDM: Minimally disruptive medicine
PAM: Patient Activation Measure
PODS: Patient-Oriented Discharge Summary
RHDS-SF: Readiness for Hospital Discharge Scale–Short Form
TDF: Theoretical Domains Framework
UBACC: University of California San Diego Brief Assessment of Capacity to Consent
